**C.5.3 Sample storage for future use**

At the end of the study, excess blood, urine and vaginal/urethral swabs samples will be stored in -70oC freezers at MU-JHU Care facilities in Mulago or at UVRI CDC laboratory in Entebbe (depending on space availability) for future testing. Tests will be done at either MU-JHU or UVRI laboratory. They may include tests to confirm previous results, to determine if participants had any sexually transmitted infections (STI) or any unprotected sex between assessment visits or to assess for the presence of STIs not tested for during the study such as HSV-2. Tests may also be done to know when exactly seroconverters became infected with HIV or STIs and to assess immunological parameters such as CD4 counts. Test results relevant to participants’ health and medical care will be given to participants and/or their doctor.

Investigators interested in using left over samples will need to submit a request to the PI who will set up an independent panel to review the scientific proposals and make recommendations to the PI before he gives his approval. The PI or any investigator requesting to use the stored samples will be asked to submit a proposal and obtain approval from the Uganda and US IRBs before using the samples. The left over samples will be stored for a minimum of two (2) years after the termination of the study. The specimen will remain the property of the PI or designee for as long as they will be stored.

**C.5.4 Cohort retention methods**

Our study power calculations account for a rate of attrition as high as 50% to ensure sufficient power for the primary endpoint comparisons[[1]](#footnote-2). Given that such a high rate carries a risk of bias, we have put in place strategies to minimize losses to follow-up as follows:

- Participants in the urban or rural site will be carefully assessed at enrolment for their mobility in order to pre-empt selective attrition
- All women and couples consenting to participate will have agreed to home visits by a study field officer.
- At the time of enrollment the field officer will make a home visit and complete a tracking locator form.
- Study retention will be monitored monthly.
- To maximize retention over 24 months of follow-up, study visits have been scheduled to coincide as much as possible with the standard ante-natal or post-natal immunization schedule and additional retention visits have been inserted so that all participants will be on a regular quarterly visit schedule.
- Every participant will be given a free calendar with visits dates marked to help them remember their appointments.
- Trained counselors will maintain regular contact with participants through calls and SMS messages while respecting participants’ schedule and privacy.
- Family and women support groups linked to both Kitgum and Mulago PMTCT programs will also help retain participants in the study by reinforcing prevention messages.
- If a participant misses a follow-up visit, a field officer or a study peer will follow up by phoning as soon as possible to reschedule the visit.
- When needed, the field officer or peer will make a follow-up visit either at the participant’s home or at an agreed upon location.

**C.5.5 Incident infections**

All participants with an incident STI or HIV infection during follow-up will receive treatment as part of standard of care provided by the hospitals and in accordance with Uganda’s National STI Treatment Guidelines[42](#_ENREF_42). These guidelines include partner notification and treatment, thus both enrolled and unenrolled partners of participants found to be infected during follow-up will be notified and treated when possible. Participants infected with syphilis and their partners will be treated with benzathine penicillin 2.4 MU IM in a single dose. Pregnant women infected with G/C or T. vaginalis and their partners will be treated with erythromycin 500mg qid for 7 days plus cotrimoxazole 2.4g bid for 3 days and metronidazole 2g single dose (no cotrimoxazole or metronidazole will be given in the first trimester or after 36 weeks of pregnancy). Non-pregnant lactating women and their partners infected with G/C or T. vaginalis will be treated with ciprofloxacin 500mg single dose and metronidazole 2g single dose plus doxycycline100mg bid for 7 days . In case of incident HIV infection in a participant, counselors will emphasize both primary & positive prevention, and a study clinician will obtain a blood sample for CD4 testing and refer the infected person(s) to Mulago or St Joseph Hospitals HIV clinic for ART eligibility assessment. All HIV seroconverters will receive cotrimoxazole prophylaxis and lifetime ART if eligible. Infected pregnant women and breastfeeding women ineligible for ART and their babies will receive PMTCT prophylaxis or treatment as per national guidelines[32](#_ENREF_32). All newly HIV-exposed infants (babies born to and/or breastfeeding from an HIV-seroconverted mother) will receive ARV prophylaxis as per national guidelines. HIV-exposed babies >6 weeks of age will be tested by HIV DNA polymerase chain reaction (PCR) assay and if infected, will be treated with triple ART at the hospital HIV clinic. Uninfected infants will be retested 6 weeks after complete cessation of breastfeeding and treated with triple ART if infected.

**C.5.6 Study participant compensation and benefits**

Mulago and Kitgum participants will be reimbursed 10,000 Ugandan Shillings and 5,000 Ugandan Shillings respectively for their time and transport to and from the clinic for each study visit that is not part of routinely scheduled visits for ante-natal, delivery or post-partum care. Participants will also be provided lunch when they will have to stay in the clinic beyond lunch time. Participants who run into hardship and have serious difficulties coming to any given visit will be dealt with on an individual basis. All participants will receive the standard of care and treatment available at the hospitals for obstetrical or medical problem at enrolment or during follow-up. Participants testing HIV-positive will receive cotrimoxazole and ARV prophylaxis for PMTCT as well as HIV/AIDS care and treatment from the hospital HIV clinic at no cost, including ART if found eligible. Provision of any care and treatment will not be contingent upon participating in or withdrawing from the study at any time.

**C.5.7 Premature study withdrawal**

Study participants will be withdrawn before the end of the follow-up period if any of the following event occurs: 1) movement out of study area for >90 consecutive days, 2) failure to attend to or to be located for >2 consecutive scheduled visits, 3) withdrawal of informed consent, 4) inability to adhere to study schedule and procedures, or 5) death of the participant. Women/couples who experience an abortion, still birth, a neonatal or infant death will be censored from follow-up but will continue to be seen by the study staff and receive care from the study clinic for 6 months following the termination of their pregnancy or the death of their child.

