**C.5.2 Postpartum intervention schedule and assessments**

After the late pregnancy visit, all women and couples in the intervention arm will be asked to return at 6 weeks and 3 months postpartum and every 3 months thereafter until the end of follow-up at 24 months postpartum or 6 weeks after the end of breastfeeding, whichever occurs first. Women and couples in the control arm will be asked to return at 3 and 6 months postpartum and every 6 months thereafter until the end of follow-up at 24 months postpartum or 6 weeks after the end of breastfeeding, whichever occurs first.

Participants randomized to the intervention arms (Arms I-2 & C-2) will receive enhanced counseling at every visit and will be retested for HIV at 3, 6, 12, 18 and 24 months postpartum (or at the end of follow-up, whichever occurs first). At these visits, both intervention and control women and men participants will undergo a physical examination and will be asked to answer individually a follow-up behavioral questionnaire about their sexual behaviors, relational and reproductive intentions, including family planning. At these same visits, all women will be bled for syphilis and HIV rapid testing and two vaginal swabs will be collected, one for G/C, and Tv testing and the other for Y chromosome detection while a blood or urine sample or urethral swab will be obtained from symptomatic men for syphilis, G/C and Tv testing [*See Schedule of Events, Appendix C*].

At the end of follow-up, all study participants irrespective of their arm assignment will undergo a physical examination, will be asked to answer individually an end-of-study questionnaire and will be bled for syphilis and HIV rapid testing and a vaginal or urethral swab will be collected for G/C and Tv testing. A vaginal swab will also be collected from women to test for the presence of Y chromosomes.

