**C.8.2 Primary analyses**

The primary analysis of the effect of the intervention on the pre-specified primary outcome will be by intent-to-treat without regard to adherence to the intervention, and will be based on pooled data from the individual and couples trials. We will compare counts of unprotected vaginal sex episodes over the last 3 months reported by each participant, including male partners in the couples trial, using log-link negative binomial models. The reporting period for these counts specified by the follow-up questionnaires will be 3 months at all visits and thus can be ignored. Robust “sandwich” standard errors will be used to account for clustering of repeated outcomes within women and couples; over-dispersion of the outcomes will be captured by the quadratic variance-to-mean parameter of the negative binomial model. To reduce potential bias from dropout, follow-up observations will be weighted by the inverse of the estimated probability of remaining in follow-up, given baseline characteristics, treatment assignment, and post-randomization factors; this approach allows us to account for informative post-randomization variables without adjusting away indirect effects of treatment . The model will allow baseline means to vary by site, sub-trial, participant gender, and visit. However, we hypothesize that the multiplicative effect of treatment on the means will be constant. To protect the type-I error rate, the primary analysis will be conducted and reported under this pre-specified hypothesis, modeling the treatment effect by the interaction of treatment assignment with an indicator for follow-up vs baseline. This assumption was used in the sample size calculation, and will be examined in augmented models allowing for heterogeneity and/or trend in the treatment effect across visits. Site, sub-trial (individual vs couples), and participant gender will be modeled as fixed effects. In secondary analyses, we will assess modification of the treatment effect by these factors, yet power will be limited; results will be reported with confidence intervals.

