***Appendix C (cont’d*) - Summary of events and measurements by study arms and visits**

|  | **Controls** | | **All** | | | **Intervention arm (ERHTEC)** | | |
| --- | --- | --- | --- | --- | --- | --- | --- | --- |
| **Follow-up** | **Standard counseling** | **Standard HIV testing & counseling** | **STI testing** | **Behavioral questionnaire, blood draws + vaginal/urethral swabs** | **Qualitative intervention assessment** | **HIV testing & enhanced counseling** | | **Risk reduction counseling,**  **Infant feeding/nutrition education & Family planning counseling** |
| Formative |  |  |  |  | **X** |  | |  |
| Baseline | **X** | **X** | **X** | **X** |  | **X** | | **X** |
| Late pregnancy | **X** | **X** | **X*** | **X** |  | **X** | | **X** |
| *6 weeks* | ***x*** |  |  |  |  |  | | ***X*** |
| 3 months | **X** | **X** | **X*** | **X** |  | **X** | | **X** |
| 6 months | **X** | **X** | **X*** | **X** |  | **X** | | **X** |
| *9 months* |  |  |  |  |  |  | | ***X*** |
| 12 months | **X** | **X** | **X*** | **X** | **X** | **X** | | **X** |
| *15 months* |  |  |  |  |  |  | | ***X*** |
| 18 months | **X** | **X** | **X*** | **X** |  | **X** | | **X** |
| *21 months* |  |  |  |  |  |  | | ***X*** |
| 24 months**+** | **X** | **X** | **X** | **X** | **X** | **X** | | **X** |
|  |  | **Measurements** | | | | |  | |

 **Retention visits:
-** Participants in the intervention arms will receive enhanced counseling but blood and vaginal swabs or urine samples will not be
 collected unless deemed necessary by the clinician.
- Participants in the control arms will receive standard counseling when study visits correspond to scheduled post-natal visits but
 will not be asked to come back otherwise until their final follow-up visit.
- No questionnaire will be administered during retention visits.

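### The missed-visit withdrawal rule counts visits, but the arms have different visit schedules, so the same postpartum absence can end outcome collection in the intervention arm and not in the control arm

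*Protocol*

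**What the plan says.** C.5.7 lists the events that end participation early. Item 2 is "failure to attend to or to be located for >2 consecutive scheduled visits". It is counted in visits, so it is met at the third consecutive miss, and it applies to both arms alike. Item 1, more than 90 consecutive days out of the study area, is counted in calendar time.

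The schedules differ by arm. In C.5.2, "all women and couples in the intervention arm will be asked to return at 6 weeks and 3 months postpartum and every 3 months thereafter", whereas "Women and couples in the control arm will be asked to return at 3 and 6 months postpartum and every 6 months thereafter". The retention-visit notes in Appendix C agree: apart from contacts that coincide with routine postnatal visits, controls "will not be asked to come back otherwise until their final follow-up visit". The same notes say "No questionnaire will be administered during retention visits", so the primary outcome is not measured at 6 weeks or at 9, 15 and 21 months.

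C.5.4 says something else: "additional retention visits have been inserted so that all participants will be on a regular quarterly visit schedule".

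For dropout, C.8.2 states that "follow-up observations will be weighted by the inverse of the estimated probability of remaining in follow-up", given baseline characteristics, treatment assignment and post-randomization factors.

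**The concern.** A rule counted in visits is neutral between arms only if the arms have the same visits. Here the intervention arm has extra visits at which nothing is measured for the primary outcome, yet missing them can count toward withdrawal. An absence that costs both arms the same single questionnaire can therefore remove an intervention participant and leave a control in follow-up.

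The primary analysis is an intent-to-treat comparison of repeated counts across all follow-up visits. If the protocol itself stops collection sooner in one arm, the later visits compare groups retained under different conditions. Part of the missing data is then produced by the rule rather than by participants.

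**Working it through.** **The plan's own figure.** The only related figure is the 80% power in C.8.5. Inputs from C.8.5:
- baseline mean 5; control follow-up mean 5 × 0.7 = 3.5; intervention follow-up mean 3.5 × 0.9 = 3.15
- over-dispersion 2, correlation 0.3, 7 assessments, 50% cumulative loss
- 410 individual women and 410 couples

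Inverting the summed X'WX gives SE(log rate ratio) = 0.0369 with linear dropout. Power = Φ(|ln 0.9|/0.0369 − 1.96) = Φ(0.1054/0.0369 − 1.96) ≈ 0.81. With constant-hazard dropout, SE = 0.0374 and power is about 0.80. The stated figure reproduces. It states no difference in loss between arms, and the point below does not depend on it.

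**Visit lists (months postpartum).**
- Intervention (C.5.2): late pregnancy, 1.5, 3, 6, 9, 12, 15, 18, 21, 24
- Control (C.5.2): late pregnancy, 3, 6, 12, 18, 24
- Outcome visits after baseline, common to both: late pregnancy, 3, 6, 12, 18, 24. With baseline these are the 7 assessments of C.8.5.

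Assumption: late pregnancy is about 1 month before delivery. An earlier late-pregnancy visit lengthens both arms' figures equally.

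**When the third consecutive miss falls** (gap = month of third miss − month last attended):

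| Last attended | Intervention | Control |
|---|---|---|
| Late pregnancy | month 6 (about 7 months) | month 12 (about 13 months) |
| 6 weeks | month 9 (7.5) | not on the C.5.2 list |
| Month 3 | month 12 (9) | month 18 (15) |
| Month 6 | month 15 (9) | month 24 (18), the final visit |
| Month 9 | month 18 (9) | no such visit |
| Month 12 | month 21 (9) | never |
| Month 15 | month 24 (9), the final visit | no such visit |
| Month 18 or later | never | never |

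Appendix C marks a 6-week standard-counseling contact for controls. If that counts as scheduled, a control last seen in late pregnancy also meets the rule at month 6 and the arms are equal there. The rows from month 3 on do not change.

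**Same absence in both arms, item 2 only.** Absences were started at quarter-month steps from month 1 to month (24 − length). The share of start dates that meets the rule is:

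| Length of absence | Intervention | Control |
|---|---|---|
| 7 months | 35% | 0% |
| 8 months | 67% | 0% |
| 9 months | 100% | 0% |
| 12 months | 100% | 20% |
| 15 months | 100% | 64% |
| 18 months | 100% | 100% |

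These are shares of start dates, not of participants.

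**Example.** A participant stays in the area but is absent from month 7 to month 16.
- Intervention: misses 9, 12 and 15 and meets the rule at 15. One outcome visit was missed (12), and months 18 and 24 are then lost. She contributes 2 of the 5 postpartum outcome visits (3 and 6).
- Control: misses only 12 and stays in. She contributes 4 of 5 (3, 6, 18 and 24).

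**If C.5.4 governed.** With quarterly visits for everyone, controls would have the intervention arm's list and the difference would be zero.

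**The case against.** Several arguments narrow the point.

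- **The schedule is contradictory.** C.5.4 puts everyone on quarterly visits, and C.5.7 does not say whether retention visits count as scheduled. On one reading the difference disappears. This stands as a reason to reconcile the text. However, C.5.2 and Appendix C are the operative schedules, and they agree that controls are not called at 9, 15 and 21 months.
- **The rule may be milder than it looks.** Item 2 can be read as requiring that the participant neither attend nor be located. C.5.4 provides calls and home visits after a missed visit, so a woman who skips counseling but is reached might not be withdrawn. The wording is ambiguous. On the milder reading the asymmetry is confined to participants who cannot be reached, and the count still runs faster in the intervention arm.
- **Item 1 is symmetric.** It is in calendar time and applies equally, so someone who moves away for 9 months can be withdrawn in either arm. A reader might infer that long absences go unnoticed among controls. C.5.4 gives monthly retention monitoring, calls and home visits without restricting them by arm, so the protocol does not support that.
- **The weights help.** They include treatment assignment and post-randomization factors. Intervention participants with the same earlier history who stay, or who return after one or two misses, can stand in for those withdrawn. To say that weighting cannot mend the problem goes too far. What stands is that it does not recover the uncollected data, and that bias remains if those withdrawn differ beyond what was measured. The dropout comparison by arm in C.8.1 would show an imbalance but not repair it.

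**Conclusion.** The point holds at moderate severity. Under C.5.2 and Appendix C, item 2 of C.5.7 makes loss of outcome data depend on arm. For participants last seen at month 3 or later, the rule is met after 9 months in the intervention arm. In the control arm it is met after 15 months, only at the final visit, or never. This assumes that counseling-only visits count as scheduled and that C.5.2 prevails over C.5.4.

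Three stronger readings are not supported:
- That the contrast is always 9 against 15 to 18 months. From late pregnancy it is about 7 against 13, or equal if the 6-week contact counts, and the 18-month case falls on the last visit, so it removes nobody early.
- That a 9-month absence never withdraws a control. A control absent from about a month before delivery to month 8 misses late pregnancy, 3 and 6 months, and meets the rule.
- That the bias favors the intervention by a known amount. This would need absence rates and the reporting behavior of returners, which the protocol does not give. Neither size nor direction can be determined.

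The stated power is unaffected.

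**What to change.** 1. Reconcile C.5.2, C.5.4, C.5.7 and Appendix C on which visits controls are scheduled for, including the 6-week contact.
2. State item 2 of C.5.7 on the outcome visits common to both arms (late pregnancy, 3, 6, 12, 18 and 24 months), or as one elapsed time that is the same in both arms. Say explicitly that counseling-only retention visits do not count, and whether a participant who is located but does not attend counts as missing.
3. Keep outcome data from any participant who returns.

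The cost is a sentence or two in C.5.7, a correction to whichever schedule text is wrong, and a little more tracing in the intervention arm. Sample size and the planned model do not change.

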**C.6 Data collection**

Quantitative data will be collected from all participants at both study sites until 24 months postpartum or 6 weeks after the end of breastfeeding, whichever comes first. Qualitative data will be collected at specific time points described in C.6.2.

**C.6.1 Quantitative data**

Data on outcomes of interests and on the individual and relational mediators of these outcomes will be collected at different time points over follow-up as outlined in Table 1 below.

**C.6.2 Qualitative data**

Qualitative data collectionwill be integral to the assessment of risk behavior and will provide insights into the feasibility and acceptability of the intervention. Focus group discussions (FGDs) will be conducted with 8-10 women and 8-10 men participants in each of the four study arms at each site at enrolment, at 9-12 months postpartum follow-up, and at the end of follow-up. Discussions will focus on the acceptability and feasibility of repeat HTC, involving male partners, the barriers and facilitators to risk reduction behavior, and the determinants of unwanted pregnancies during breastfeeding. We will use theoretic selection for maximum variability in responses. FGDs will also be conducted with 4 midwives and all study counselors at each site, once at baseline and once at the end of follow-up and will focus on the acceptability and feasibility of repeat HTC and of involving male partners.

[figure not shown]

**C.7 Measures**

**C.7.1 Primary outcomes**

The primary outcomes are the frequency of unprotected sex and the incidences of HIV and STI over follow-up. The trial is powered to detect a 10% difference in the frequency of unprotected sex[[2]](#footnote-3) accounting for a 50% loss to follow-up over 2 years. The frequency of unprotected sex will be determined as the self-reported number of episodes of unprotected vaginal intercourse with inconsistent or no condom use in the last 3 months and will be validated by Y chromosome detection in vaginal swabs. Reports by each partner in the couple trial will be treated as two correlated outcomes.

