**Study outcomes**

Formative research outcomes:

Perceptions, attitudes, expectations and potential barriers about men involvement in (MNCH care, and an ERHTEC intervention.

Primary outcomes for the randomized trial

Comparison of unprotected sex frequency, and HIV and STI incidence rates among intervention (ERHTEC) and control (standard WHO recommendation) arms .

Cost-effectiveness of the ERHTEC intervention compared to standard of care

Secondary outcomes for the randomized trial

Comparison of unintended recurrent pregnancy rates across study arms

Associations of individual and dyadic variables with the primary and secondary outcomes

Maternal and infant mortality rates

Additional study outcomes

Trial participants’ and staff’s experiences and perceptions about the intervention

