**Stratified randomized trial**

Participant screening, enrolment & randomization (N=1,230 HIV-negative women)

** Kitgum District Hospital will be only used if trial participant
accrual from St Joseph Hospital is insufficient*

Arm C-2* - Extended repeat HIV retesting and enhanced counselling (ERHTEC)

Couples (N=205 women and 205 men)

Primary outcomes**:

- Rates of unprotected sex, and HIV and STI incidences

- Costs and cost-effectiveness of the intervention

Secondary outcomes**:

- Rates of unintended recurrent pregnancies

- Associations of individual and dyadic variables with primary and secondary outcomes

- Maternal and infant mortality rates

- MTCT of HIV among women acquiring HIV during follow-up

Additional outcomes:

- Acceptability/feasibility, and barriers/facilitators of the intervention

** I-1 = individual control arm / I-2 = individual intervention arm / C-1 = couple control arm / C-2 = couple intervention arm*

*** Both primary and secondary outcomes will be assessed at the end of follow-up, defined as 24 months postpartum or 6 weeks after the end of breastfeeding, whichever occurs first*

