**205 women receive ERHTEC in late pregnancy + at 3,6,12, & 18 mos post-partum**

**205 couples receive repeat HTC in late pregnancy**

**205 couples receive ERHTEC in late pregnancy + at 3,6,12, & 18 mos post-partum**

**Arm I*-1**

**Arm I*-2**

**Arm C*-1**

**Arm C*-2**

**** I = Individual; C = Couple***

Follow-up will end at 24 months postpartum or 6 weeks after the end of breastfeeding, whichever occurs first. Quantitative data will be collected on participants’ HIV and STI status, socio-demographics characteristics, risk behaviors and perceptions, as well as relational factors and reproductive history and intentions. The primary outcomes will be the frequency of unprotected sex and the incidences of HIV and STI over follow-up. Self-reports of unprotected sex by women participants will be validated by testing women for the presence of semen biomarkers (Y chromosome) in vaginal swabs[36](#_ENREF_36). We will also collect qualitative data at baseline and at the end of follow-up on the knowledge, perceptions and experiences of study participants and providers on the challenges of retesting, partner’s involvement and primary HIV prevention.

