**Scalability:**

What services do participants expect to receive as part of routine MNCH/PMTCT care after having experienced the ERHTEC intervention?

1. This was done in response to a comment raised by a NIH reviewer who stated: *“[…] it is not clear how feasible it is to follow up couples for two or more years. […] The question is attrition rate over time – the power analysis assumes 30%, but a sensitivity analysis up to 50% would be a good idea“.* In response to this comment, we increased our attrition assumption in our sample size calculation from 30% (original submission) to 50% to ensure sufficient power for the primary endpoint comparisons.: [↑](#footnote-ref-2)
2. The study could not be powered on HIV incidence because the sample sizes required to detect significant decreases in HIV or STI incidences would be too large given the baseline incidence estimates in the population to be studied. The current estimated annual incidence of HIV in pregnant women in Uganda is <2% while syphilis, Gonorrhea/Chlamydia and Trichomonas vaginalis prevalence rates are <4% among HIV-negative women, resulting in sample sizes >2,500 for a 30% reduction over 2 years, which is beyond the scope of this study. We also considered a composite STI primary endpoint but the sample size remained >1,500. [↑](#footnote-ref-3)

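### The protocol calls three outcomes primary, and cost-effectiveness too in two places, but sets error rate and power for only one of them

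*Protocol*

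**What the plan says.** Four places in the protocol list the primary outcomes.

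- C.7.1: "The primary outcomes are the frequency of unprotected sex and the incidences of HIV and STI over follow-up".
- C.1 gives the same three: "The primary outcomes will be the frequency of unprotected sex and the incidences of HIV and STI over follow-up".
- The Protocol Summary, under study outcomes, has the same three and adds "Cost-effectiveness of the ERHTEC intervention compared to standard of care".
- The Schema does likewise, adding "Costs and cost-effectiveness of the intervention".

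The statistical sections read differently.

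- C.8.2 uses the singular: "The primary analysis of the effect of the intervention on the pre-specified primary outcome will be by intent-to-treat". The test it then describes is a negative binomial comparison of counts of unprotected vaginal sex, pooled over the individual and couples trials.
- Its statement on error control is "To protect the type-I error rate, the primary analysis will be conducted and reported under this pre-specified hypothesis". That sentence concerns the assumption of a constant treatment effect in the unprotected-sex model. It does not address a set of several primary outcomes.
- The last paragraph of C.8.2, still under primary analyses, adds a logistic model for STIs and a pooled logistic model for HIV, with no significance level for either.
- C.8.5 gives a two-sided 5% error rate and 80% power for a 10% reduction in unprotected-sex episodes, and for nothing else.
- Footnote 2, attached to C.7.1, begins: "The study could not be powered on HIV incidence because the sample sizes required to detect significant decreases in HIV or STI incidences". It puts the required size above 2,500 for a 30% reduction, and above 1,500 for a composite STI endpoint. The trial enrols 820 women and 410 male partners.

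**The concern.** Which outcome is primary is decided in the protocol, and here the outcome lists and the statistical sections give different answers. The lists give HIV and STI incidence the same standing as unprotected sex. The statistical sections plan a confirmatory test for unprotected sex alone.

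This matters in two ways. A chance finding on STI or HIV incidence could be reported as a positive primary outcome, since C.7.1 calls it one. Conversely, an inconclusive HIV result, which footnote 2 already leads one to expect, could be read as a negative primary outcome. The protocol intends its findings to inform national policy, so the standing of each result should be clear before the data are seen.

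**Working it through.** **1. The plan's own figure.** Inputs from C.8.5: 410 individual women and 410 couples; 7 assessments including baseline; correlation 0.3 within person and within couple; 50% cumulative loss; baseline mean of 5 episodes; 30% control-arm reduction; over-dispersion 2; 10% net effect. Allocation is 1:1.

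Following the method described there, with dropout spread over follow-up and a treatment main effect in the model, the standard error of the log rate ratio is 0.0369 (linear dropout) or 0.0374 (exponential dropout).

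- Power = Phi(|ln 0.9| / SE - 1.96), with |ln 0.9| = 0.1054
- Linear: Phi(2.85 - 1.96) = 81.4%
- Exponential: Phi(2.81 - 1.96) = 80.3%

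The stated 80% is reproduced for unprotected sex tested alone at two-sided 5%. Other readings of the model (no treatment main effect, all dropout immediately after baseline, a product-type couple correlation) give 63% to 92%. The reading closest to the text gives 80-81%.

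**2. Error rate if any one of three tests counts as success.** The protocol states no such rule, so this is conditional. Each test is taken at two-sided 5%.

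| Correlation between tests | Family-wise error |
|---|---|
| 0 (1 - 0.95^3) | 14.3% |
| 0.3 | 13.6% |
| 0.5 | 12.5% |
| 0.8 | 9.9% |
| Upper bound (3 x 5%) | 15% |

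The correlated rows come from simulating equally correlated normal test statistics. Cost-effectiveness has no hypothesis test in C.8.4 and adds nothing. C.8.2 does not say whether the STIs form one test or several; four independent tests would give 1 - 0.95^4 = 18.5%.

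**3. Power for HIV incidence.** The control rate is set at 2 per 100 person-years, the ceiling of footnote 2's figure for Uganda (below 2% a year), with a 30% reduction. Person-years are assumed: from 820 (half of full follow-up) to 1,640 (820 women for 2 years), women only.

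- Expected events = (person-years / 2) x 0.02 x (1 + 0.7): 13.9 at 820 and 27.9 at 1,640
- Power = Phi(sqrt(events)/2 x |ln 0.7| - 1.96): 9.8% and 15.4%
- Events for 80% power = 4 x (1.96 + 0.8416)^2 / (ln 0.7)^2 = 247

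As a cross-check on proportions, 4% against 2.8% over 2 years needs about 3,580 women per arm for 80% power, consistent with footnote 2's figure. Power is about 16% with 410 women per arm and about 10% with 205.

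**4. The two ways to resolve it.** With unprotected sex as the single primary outcome, error stays at 5% and power at about 80% with the planned sample. Splitting 5% equally over three outcomes (1.67% each, critical value 2.394) gives power for unprotected sex of Phi(2.80 - 2.394) = 66% starting from exactly 80%, or Phi(2.85 - 2.394) = 68% starting from 81.4%. Keeping 80% would take ((2.394 + 0.8416) / (1.96 + 0.8416))^2 = 1.33 times the information.

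**The case against.** The strongest reply is that the protocol does identify its confirmatory test. C.8.2 refers to one primary outcome and then specifies its model, population and estimation. C.8.5 sizes the trial on it alone. In C.7.1 the sentence after the three-outcome list says the trial is powered on unprotected sex, and footnote 2 explains why the other two were not used for sizing. Read this way, the error rate is 5% and the word primary is merely used loosely. As a reading of intent this stands. It does not remove the conflict, because four outcome lists say otherwise and C.8.2 itself keeps the HIV and STI models under primary analyses.

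A reader might go further and infer that the protocol has no defined basis for success, or that its error rate is 14%. The documents support neither. C.8.2 and C.8.5 point to unprotected sex. The 14% needs an any-of-three rule and independent tests, and the protocol states neither. Independence is also doubtful, since the outcomes are measured in the same people and unprotected sex is a route to the other two.

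Three further replies are fair.

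- The order of testing and allocation of alpha may sit in a statistical analysis plan that is not shown, so their absence is not the point here. The conflict over what is primary lies within the protocol.
- The low HIV power is not hidden: footnote 2 discloses it. The abstract and introduction also cite 2 to 17 infections per 100 person-years across sub-Saharan Africa, of which 2 is the low end. The calculation uses footnote 2's figure because it is specific to Uganda and is the one used for sizing.
- Preventing HIV is the stated goal of the study, so the sponsor may prefer to keep HIV and STI incidence prominent. That is compatible with the fix, provided one outcome is named as confirmatory.

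**Conclusion.** The protocol contradicts itself on what is primary: three outcomes in C.1 and C.7.1, those three plus cost-effectiveness in the Summary and Schema, and one in C.8.2 and C.8.5. The intended confirmatory outcome can be inferred, but the outcome lists do not state it, and two outcomes declared impossible to power carry the primary label.

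The consequence for error is conditional. It is about 14% if success on any one of three independent two-sided 5% tests were claimed, about 10-14% for correlations from 0.8 down to 0.3, and at most 15% for three tests. If unprotected sex alone is confirmatory, it is 5%. Power for a 30% reduction in HIV incidence is about 10-16%, assuming 2 infections per 100 person-years and between half and all of the planned woman-years. A rate below 2 would lower it further.

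**What to change.** - In the Protocol Summary, Schema, C.1 and C.7.1, state that the frequency of unprotected sex is the sole primary (confirmatory) outcome, tested at two-sided 5%.
- In the same four places, list HIV and STI incidence as key secondary outcomes, reported as estimates with confidence intervals.
- In C.8.2, move the HIV and STI models out of the primary analysis, for example to C.8.3.
- In the Summary and Schema, list cost-effectiveness as a separate objective under Aim 3.

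The cost is a protocol amendment in wording only. The sample size, the 5% error rate and the stated 80% power are unchanged. What the sponsor gives up is the ability to base a primary claim on HIV or STI incidence, for which footnote 2 says the trial could not be powered.
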